## Abstract

**Introduction:**

Preschool wheeze and asthma are associated with substantial morbidity and impaired future lung function. Yet, wheeze is unreliably reported with high disagreement (>50%) between parental and physician observations. Objectively defining wheeze and its reversibility could enable an earlier asthma diagnosis and improve preschool wheeze management.

Our primary aim is to determine in preschool children (aged 0.5–6 years) suspected of asthma whether adding WheezeScan to routine clinical assessment (vs assessment without WheezeScan) improves the diagnosis of asthma. Our primary hypothesis is that using WheezeScan in preschool children suspected of asthma is associated with increased definitive asthma diagnoses in this age group. Our secondary aims are to (a) examine the effect of using WheezeScan on patient-reported outcomes (PROs) and (b) healthcare costs. Our secondary hypothesis is that using WheezeScan in preschool children suspected of asthma is associated with improved quality of life without incurring additional healthcare costs.

**Methods and analysis:**

Our multicentre prospective cohort study involves recruiting 102 preschool children suspected of asthma. WheezeScan, a user-friendly digital device, incorporates artificial intelligence to objectively define wheeze and its response to bronchodilators. Over 6 weeks, parents/caregivers use the WheezeScan two times per day and whenever wheezing is suspected. If wheeze is detected, an inhaled short-acting β_2_-agonist is administered and WheezeScan determines if wheeze resolves thereafter.

Our primary endpoint is the proportion of children with a definitive asthma diagnosis, compared with baseline, based on the treating clinician’s assessment using WheezeScan data. Our secondary outcomes are PROs, reflecting generic health-related quality-of-life and cough-specific (if chronic cough present) outcomes and health costs.

**Ethics and dissemination:**

The Children’s Health Queensland Human Research Ethics Committee (HREC/23/QCHQ/100691) and the Queensland University of Technology Office of Research Ethics and Integrity approved the study. We will publish and share results with the academic and healthcare communities and relevant patient organisations.

**Trial registration number:**

Australian New Zealand Clinical Trials Registry ACTRN12623000904673.

WHAT IS ALREADY KNOWN ON THIS TOPICRecurrent wheeze affects about 30–40% of preschool children, causing considerable morbidity, healthcare utilisation and costs, while also being associated with future lung function impairment. Approximately one-third of children with recurrent preschool wheeze are diagnosed with asthma later in childhood.WHAT THIS STUDY ADDSThis world first multicentre study seeks to address the need in preschool children to identify wheeze and reversible airway obstruction (RAO) accurately by using recently developed digital technology that objectively determines the presence or absence of wheeze. In so doing, it will also assess whether improving the diagnosis and management of RAO and asthma is associated with improved clinical and patient-reported outcomes without increasing healthcare costs.HOW THIS STUDY MIGHT AFFECT RESEARCH, PRACTICE OR POLICYIdentifying preschoolers with asthma from other causes of wheezing in this age group will fulfil a large unmet clinical need and research gap identified by our parents and Parent Advisory Group, as well as by an Australian and an international survey of clinicians and/or parents/caregivers.

## Introduction

 Wheeze is a continuous, usually high-pitched, breath sound accompanied by a prolonged expiratory phase in the respiratory cycle. It originates from air turbulence in the lower airways due to partially obstructed intrathoracic airways causing flow limitation.^1^ Important aetiologies in young children are acute lower respiratory infections (including bronchiolitis), asthma, an inhaled foreign body and other lower airway disorders. Up to 50% of children have had an episode of wheeze by the time they reach school age, with 30–40% experiencing further wheezing episodes.^2^ Irrespective of the underlying wheezing pathobiology, wheeze symptoms cause substantial morbidity^3^ and economic cost.^2^ In the USA, preschoolers with recurrent wheeze have approximately two times the rate of outpatient physician and emergency department visits for wheeze exacerbations and more than five times the hospitalisation rate of older children with known persistent asthma.^4^ Furthermore, preschool wheeze is also associated with future impaired lung function trajectories, even when the wheeze is transient.^5^

When children are old enough to perform spirometry, many with a history of recurrent wheeze as preschoolers demonstrate a clear pattern of reversible airway obstruction (RAO) after receiving an inhaled short-acting β_2_-agonist (SABA) and/or inhaled corticosteroids, thereby suggesting they have underlying asthma.^6 7^ A systematic review and meta-analysis^8^ that included 19 studies (n=1022 children) concluded ‘inhaled SABA treatment for acute wheeze/asthma symptoms showed beneficial effects in young children and infants’. The meta-analysis found treatment with inhaled SABAs in preschoolers with wheeze decreased respiratory and wheeze scores, decreased respiratory rate and increased oxygen saturation.^8^ Within 60 min of administering SABA, the standardised mean difference between groups (all favouring those on SABA) was: decreased respiratory score (−2.05 points, 95% CI −2.50 to –1.59), decreased respiratory rate (−0.86, 95% CI −1.30 to –0.41), increased oxygen saturation (0.56, 95% CI 0.16 to 0.95), decreased respiratory work (−0.80, 95% CI −1.60 to –0.00) and decreased wheezing score (−1.07, 95% CI −1.80 to –0.33). In the subgroup analyses of children aged <2 years, the systematic review found similar significant effects for all outcomes.^8^ Thus, it is unsurprising that preschool children with recurrent wheeze and symptomatic improvement following SABA treatment will be diagnosed with asthma and, in some cases, their history of wheeze may date back to infancy.^9^ Under these circumstances, asthma therapies are generally used, although there is substantial variability between guidelines,^3^ probably due in part to the lack of evidence and problems with objectively defining wheeze.

Nevertheless, current guidelines for diagnosing asthma recommend objective confirmation with spirometry or peak flow,^10^,^12^ although the exact criteria vary among guidelines. Effectively, the change in spirometry or peak flow represents objective documentation of RAO, the hallmark for diagnosing asthma. Lung function indices are rarely available for young children, and so in preschoolers, finding clinical evidence suggestive of RAO (ie, resolution of dyspnoea or wheeze with inhaled SABA)^13 14^ is often used as a surrogate measure. Nevertheless, this approach remains controversial as it requires accurate and objective detection of wheeze but often relies on parental detection and reporting.^3^

Despite the importance of detecting wheeze, there are high levels of disagreement (>50%) between parental and physician reporting of wheeze.^15^ This may cause underdiagnosis or overdiagnosis of asthma and lead to overuse or underuse of medications, children undergoing unnecessary procedures and high parental anxiety.^16 17^ Crucially, failing to recognise wheeze can delay diagnosis, especially if wheeze is recurrent, as it can defer appropriate treatment, which may lead to ongoing exacerbations, doctor visits, hospitalisations and an increased burden on parents/caregivers. In contrast, early recognition and treatment of asthma improves symptoms and quality of life (QoL).^10^,^12^

While detecting wheeze and its reversibility with SABA is not the sole predictor in the diagnostic journey for asthma in preschool children, it is still a crucial step. Addressing the poor reliability of detecting wheeze in young children^15 18^ is a clear clinical gap. Recently, this gap was highlighted by the European Respiratory Society (ERS) Taskforce statement on preschool wheezing disorders.^5^ Its importance is even greater in settings where reporting of respiratory symptoms is more challenging, such as in disadvantaged First Nations communities^19^ and in settings where there are diverse cultures and languages spoken.^18^

Reliable and objective detection of wheeze using digital technology in clinics during face-to-face visits and at home when applied by parents could lead to improved diagnosis from detecting wheeze that responds to asthma treatments. There are now clinically validated tools that can objectively define wheeze. One such tool is the WheezeScan (figure 1, Omron Healthcare, Japan), which is the world’s first clinically validated device^20^ that uses artificial intelligence to detect and differentiate wheeze from other breath sounds in young children aged 4 months to 7 years.^21^ For our study, we chose WheezeScan as its design is user-friendly, ergonomic, light and portable, allowing parents to have it with them at all times and to remove any uncertainty when breathing distress occurs. In a pilot study from Germany involving 20 children, parents detected wheeze in 22/708 (3.1%) routine two times per day recordings, but WheezeScan indicated wheeze was present in 140/708 (19.8%) of the recordings.^20^

**Figure 1 F1:**
[figure not shown]
WheezeScan (Omron Healthcare, Japan). WheezeScan is the device we are using in our study. It is the world’s first clinically validated device^20^ that uses artificial intelligence to detect and differentiate wheeze from other breath sounds in young children aged 4 months to 7 years.

In addition to detecting wheeze accurately to allow an earlier and more objective diagnosis of asthma in preschool children,^5^ having patient-reported outcomes (PROs) as trial endpoints is important for adoption of effective best practice, which is also relevant to patients and their families. PROs include parent’s perception of their own and their child’s QoL, and in the case of WheezeScan with its ease of use. Disadvantaged Indigenous children and those with cultural and language barriers have a higher burden of respiratory illnesses than other children in the community^22^ and, for equity, studies should make every effort to include these children, irrespective of obstacles that may arise.

Therefore, with so many gaps^5^ in the understanding and management of preschool wheeze, both clinicians and parents are left confused over whether or not wheeze is present in young children, if it indicates underlying asthma and, if so, how it should be treated.^16^ Our study addresses several of these key clinical and end-user identified gaps.

## Aims and hypotheses

Our primary aim is to determine in preschool children (aged 0.5–6 years) suspected of asthma whether adding WheezeScan to routine clinical assessment (vs assessment without WheezeScan) improves the diagnosis of asthma. Our primary hypothesis is that using WheezeScan in preschool children suspected of asthma is associated with increased definitive asthma diagnoses in this age group.

Our secondary aims are to examine the effect of using WheezeScan on: (a) PROs and (b) healthcare costs. Our secondary hypothesis is that using WheezeScan in preschool children suspected of asthma is associated with improved QoL without incurring additional healthcare costs.

Additionally, we aim to evaluate the perceived usefulness of WheezeScan for parents/caregivers using a qualitative evaluation.

## Methods and analysis

### Design

We are undertaking a prospective multicentre cohort study. Recruitment commenced from 1 February 2024 and is continiuing.

### Study settings and participants

#### Study sites

Our study sites are the: Queensland Children’s Hospital (Brisbane, Queensland and including Indigenous outreach clinics in rural and remote Queensland), Gold Coast University Hospital (Gold Coast, Queensland), Children’s Hospital at Westmead (Sydney, New South Wales) and Royal Darwin Hospital (Darwin, Northern Territory), all in Australia.

#### Inclusion criteria

Children (aged 0.5–6 years) undergoing review by paediatric specialists for suspected asthma (≥2 reported wheeze episodes, chronic (>4 weeks) dry cough or exertional breathlessness) and have ongoing symptoms.

#### Exclusion criteria

Exclusion criteria are: (a) current chronic wet cough, (b) previous specialist-diagnosed asthma, (c) previously enrolled, (d) unable to complete PROs or (e) participating in another trial with an active intervention that may affect or bias findings.

#### Recruitment

Eligible children are identified from general paediatric and respiratory clinics and the emergency department at each study site. At each site, those fulfilling the inclusion criteria are invited to participate in the study and informed consent is sought before enrolment. On obtaining informed consent, baseline data are collected, and a specialist clinical review is performed. The study flow is presented in figure 2 and the outline of procedures is summarised in table 1.

**Figure 2 F2:**
[figure not shown]
Study flow of our cohort study. Dx, diagnosis; FeNO, fractional exhaled nitric oxide; ICS, inhaled corticosteroids; PC-QoL, Parent Cough-Specific Quality-of-Life^29^; PedQL, Paediatric Quality-of-Life Inventory V.4^28^; PROs, patient reported outcomes; wks, weeks.

**Table 1 T1:** Outline of study procedures

Assessment	Baseline (T1) At enrolment or prior to starting study	From baseline	
		2 weeks T2	6 weeks T3
	Window:	±4 days	±4 days
Screening for eligibility	✓		
Informed consent	✓		
Sociodemographic and medical history	✓		
Medical chart review	✓		
Clinical assessment	✓	✓ (optional)	✓ (optional)
Classify asthma (yes/possible/no)	✓ (primary specialist clinician)	✓ (primary specialist clinician)	✓ (primary and independent specialist clinicians)
PedsQL^28^	✓	✓	✓
PC-QoL^29^ (if chronic cough present)	✓	✓	✓
Health surveillance questions		✓	✓
Spirometry (if aged >4 years); pre-SABA and post-SABA where possible	✓	✓ (if seen)	✓ (if seen)
FeNO (if aged >4 years) once during study, if possible	✓	✓ (if seen)	✓ (if seen)
Analyse WheezeScan data		✓	✓
Parent WheezeScan utilisation question*			✓
NASSS-informed qualitative interviews		✓	or ✓
Collect results for full blood count, RAST, IgE (if available as part of clinical request)†	✓		or ✓
Contact parent—general health and WheezeScan questions about any problems encountered	Every week between T1 and T3		

* Parent utilisation question ‘The WheezeScan is useful in managing my child’s wheezing problem’ 5-point Likert (range from 1=strongly disagree to 5=strongly agree).

† Recorded for possible future studies.

FeNO, fractional exhaled nitric oxide; IgE, Immunoglobulin E; NASSS, non-adoption, abandonment, scale-up, spread and sustainability; PC-QoL, Parent Cough-Specific Quality-of-Life; PedsQL, Paediatric Quality-of-Life Inventory V.4; RAST, radioallergosorbent test; SABA, short-acting β2 agonist.

## Study protocol

### Data collection

Data are recorded by good clinical practice (GCP) trained researchers on case report forms as per our many trials.^23^,^27^

#### At baseline (timepoint 1 (T1))

We are collecting study PROs (Paediatric Quality-of-Life Inventory V.4 (PedsQL)^28^ (in all children) and Parent Cough-Specific Quality-of-Life (PC-QoL)^29^ (if chronic cough present) questionnaires, as done previously^23^ and sociodemographic and clinical data (eg, age, sex, family/household size, personal and family history of atopy, ethnicity (eg, First Nations), medications used, tobacco or e-cigarette exposure and immunisation history) from the parents/caregivers, medical notes and the Australian Immunisation Register.

As per routine practice, children are assessed clinically by a paediatric specialist, most of whom are respiratory specialists. Those who are classified as ‘definite yes’ receive routine clinical treatment and are not seen again until timepoint 3 (T3). All children have the WheezeScan applied and if wheeze is present, the child is given 400 µg (four puffs) of inhaled SABA (using a spacer±mask), the standard dose to define presence/absence of a bronchodilator response.^11^ After 10 min, the WheezeScan is used again to determine whether wheeze is still present and the results recorded. Whenever possible, fractional exhaled nitric oxide (FeNO) is measured, but the clinician is blinded to the result.

A member of the research team then teaches the parents/caregivers of those classified as ‘possible’ and ‘definite no’ how to use the WheezeScan and the e-diary, both of which are to be used routinely two times per day for the next 2 weeks and when wheeze is suspected by the parents/caregivers (eg, postphysical activity). The parents/caregivers are asked to give 400 µg of inhaled SABA (using a spacer±mask) if wheeze is detected and to then reapply WheezeScan 10 min later to determine and record whether RAO is present. If wheeze is still present, the parents are asked to give a further 400 µg of inhaled SABA (as above), and then to reapply WheezeScan again 10 min later, and record whether RAO is present.

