### Endpoints

#### Primary

Proportion of children with a definite diagnosis (yes/no) of asthma from T3 to T1, based on the classification provided by the treating specialist clinician.

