#### Analyses

For the primary aim we will compare the proportions using McNemar’s test.

For the secondary aims:

Concordance of asthma classification (definite yes, definite no, possible) between the treating clinician and the independent specialist will be undertaken using weighted Kappa. Likewise, concordance between clinician and WheezeScan detected wheeze will be undertaken using Cohen’s Kappa.Change in PROs scores will be presented as means and SD and assessed by paired t-tests (assuming normal distribution) and the proportions with scores above the minimal clinically important difference (MCID) for each PRO in each group defined at T3 compared with T1.Composite measure of ‘usefulness of WheezeScan’ will be described and presented as numbers and percentages.Healthcare resource use associated with respiratory healthcare will be costed using actual costs (when known) or market rates from the perspectives of the healthcare system provider and families for each pathway (figure 2). Uncertainty estimates will be generated using bootstrap resampling (10 000 replications).

We anticipate reporting the last two secondary aims in a separate paper, as there will be a delay in the healthcare resource use analysis.

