#### Sample size estimates

Our sample size is 102 children. This is based on conservative estimates of 15% being diagnosed with asthma at T1 and 30% at T3, with a correlation between the paired observations of 25%, which provides power>80% to detect a difference of 15% between the proportions. We will replace children with incomplete data and thus we expect to have complete data from 102 children. We conservatively estimate that 33% of children in our target group (preschool children with recurrent wheeze) have asthma (defined as RAO) and when adequately treated will be two times as likely to have significantly improved PRO above their MCID compared with when not treated due to wheeze misclassification known to be >50% in this age group.^15^

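### The T1 label is both the baseline of the primary endpoint and the gate to home WheezeScan monitoring, so a label left at 'possible' in expectation of device data would lower the baseline

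*Protocol article*

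**What the plan says.** The Aims section compares routine assessment with WheezeScan against assessment without it. There is no control arm, so the T1 classification alone represents the second condition. The primary endpoint is the "Proportion of children with a definite diagnosis (yes/no) of asthma from T3 to T1, based on the classification provided by the treating specialist clinician", and for its analysis "we will compare the proportions using McNemar"'s test.

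Under At baseline (T1), the same label sets the pathway. Children labelled 'definite yes' "receive routine clinical treatment and are not seen again until timepoint 3 (T3"). For the rest, "A member of the research team then teaches the parents/caregivers of those classified as" 'possible' or 'definite no' to use the device at home twice daily, and under Follow-up (T2) those data are reviewed after two weeks.

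Under Outcomes and endpoints, the T2 and T3 labels have stated definitions based on device-documented wheeze and its response. The T1 label rests on the treating specialist's clinical parameters, which are not listed. The only blinding described for that clinician is to FeNO. The independent specialist classifies at the end of the study, so that review does not check the T1 label. WheezeScan is also applied once in clinic at T1 to every child, whatever the label.

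**The concern.** One judgement does two jobs: it is the comparator value and it allocates home monitoring. A clinician hesitating between 'definite yes' and 'possible' knows that 'possible' brings two weeks of home recordings and a review. A label given in that knowledge need not be the one that would be given if no device data were coming, and the latter is what the aim calls for.

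A child moved from 'definite yes' to 'possible' at T1 lowers the baseline whether the endpoint is read as 'yes' only or as 'yes or no'. If that child is then definite at T3, the primary analysis counts a gain for WheezeScan that routine assessment would have delivered at T1. The judgement that was not recorded at T1 cannot be recovered by any later analysis.

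**Working it through.** **Inputs.** All from Sample size estimates: N = 102; planning rates of "15% being diagnosed with asthma at T1 and 30% at T3"; a paired correlation of 0.25; and claimed power above 80% for a 15-point difference. The article states neither alpha nor the version of McNemar's test. I assume two-sided 0.05 and show the versions separately.

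**1. The plan's own figure.**
- Both positive: p11 = 0.15×0.30 + 0.25×√(0.15×0.85×0.30×0.70) = 0.045 + 0.25×0.1636 = 0.0859.
- Forward moves (not yes to yes): 0.30 − 0.0859 = 0.2141, or 21.8 of 102.
- Reverse moves (yes to not yes): 0.15 − 0.0859 = 0.0641, or 6.5 of 102.
- Discordant: 0.2141 + 0.0641 = 0.2782.
- Connor's formula: z = (0.15√102 − 1.96√0.2782) / √(0.2782 − 0.15²) = 0.95, so power is 82.9%.
- By enumeration, power is 85.5% (uncorrected), 83.7% (mid-p), 79.3% (exact) and 79.2% (continuity-corrected).

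The stated power above 80% is reproduced, within a point for the two conservative versions.

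**2. Six deferrals, no other change.** With b forward and 0 reverse moves, exact two-sided p = 2×0.5^b.
- b = 5: p = 0.063. b = 6: p = 0.031.
- For 6 v 0, the continuity-corrected p is 0.041 and the uncorrected p is 0.014. The uncorrected test already reaches p = 0.046 at 4 v 0.

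**3. Adding reverse moves.**
- 6 v 1: exact p = 0.125, corrected 0.131, uncorrected 0.059. None is significant.
- With 6 reverse moves, significance needs 17 forward moves (exact) or 15 (uncorrected). With 7 reverse moves it needs 18 or 17.
- If background moves balance at 6 or 7 each way, the deferrals needed on top are 17 − 6 = 11 or 18 − 7 = 11 (exact), and 15 − 6 = 9 or 17 − 7 = 10 (uncorrected).

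Reverse moves are possible: 'definite yes' children are reclassified at T3 and, on the yes/no reading, a 'definite no' can become 'possible'.

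**4. Chance of a significant result with six deferrals and no true effect.** Six children are fixed as forward moves, and the other 96 move at equal background rates each way (exact test).
- 6.4% each way: about 19% (18.7% simulated, 18.9% by full enumeration).
- 1% each way: about 47% (46.7% simulated, 47.6% by full enumeration).

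The nominal level is 5%.

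**5. Share of eligible children.** Only a child who would otherwise be 'definite yes' can be deferred. If the planned 15% is the rate without deferral, that is 0.15×102 = 15.3 children. Six deferrals are then 6/15.3 = 39% of them, and 9 to 11 are 59% to 72%.

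**The case against.** **Opposing incentive.** 'Definite yes' children have routine treatment from T1, while for the others the protocol's inhaled corticosteroid step follows the T2 review. A clinician convinced of asthma thus has a reason not to defer. This stands, and it makes deferral more plausible for uncertain children than for clear ones.

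**Deferral is not shown.** A reader might infer that clinicians are deferring diagnoses, or that the primary result will be an artefact. The article supports neither. It shows an opportunity and gives no rate.

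**Six is a best case.** A reader might infer that six deferrals are enough to make the trial positive. That holds only if all six are definite at T3 and no child moves in reverse. Deferred children can also end as 'possible' or, on the 'yes' reading, as 'definite no', and then they are not gains. As a share of the roughly 15 children planned as diagnosed at T1, the numbers needed are large.

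This too stands, with one qualification. A reverse rate of 6.4% means that 0.0641/0.15 = 43% of children labelled 'yes' at T1 lose the label by T3. If fewer do, the number of deferrals needed falls towards six.

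**The device is not withheld from 'definite yes' children.** All have it applied in clinic at T1. The label decides home monitoring and T2 review only.

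**Routine judgement is the comparator, and the full protocol or forms may say more.** Unstructured specialist judgement is a fair picture of routine care, and the supplemental file and case report forms are not shown. The point therefore does not rest on missing criteria. It rests on the dual role of the label, which the article states.

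**Already acknowledged.** The limitations section admits a risk of bias from the cohort design, but does not mention this route.

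**Conclusion.** The point holds as a weakness the design permits, not as a demonstrated bias. The T1 label is both the sole comparator and the gate to home monitoring, and the clinician who sets it knows this. Deferring a likely 'definite yes' can only lower the baseline, and it adds to the apparent gain when the child is definite at T3.

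The size is conditional. Six deferrals suffice under the exact test with no reverse moves, and 9 to 11, depending on the test version, at the reverse rate the sample-size assumptions imply. Even where six do not guarantee significance, they raise the chance of a false positive to about 19% at that rate and about 47% at 1% each way. These figures assume two-sided 0.05, balanced background moves and deferred children who all become definite. The true deferral rate is unknown. It merits a cheap improvement and does not invalidate the study.

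**What to change.** For children still to be enrolled (the Design section says recruitment is continuing):

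1. Word the T1 classification as the diagnosis the clinician would make today if no WheezeScan information were to follow.
2. Have it signed and locked before the in-clinic WheezeScan reading and before the pathway is assigned.
3. Record on the same form a 0–100% clinical probability of asthma.
4. In the statistical analysis plan, which the article says is still to be developed, pre-specify a sensitivity analysis before data are seen. It should count T1 'possible' children above each of a range of fixed probability cut-offs as 'definite yes' at T1. Report it beside the primary result, and identify children enrolled before and after the change.

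The cost is one sentence and one field on the T1 form, plus a short notice to sites. No extra visit or assessor is needed, and no treatment changes. There are three drawbacks. Children already enrolled cannot be relabelled. The same clinician still knows the pathway rule, so the bias is reduced or measured but not removed. The observed increase may be smaller.
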